**Methods:**

The study will employ a mixed-method feasibility randomized controlled trial design. Forty individuals with type 2 diabetes will be randomly allocated to treatment and control groups using block randomization. The primary feasibility outcomes include acceptability, eligibility, recruitment, and participant retention rates, which will be computed using descriptive analysis. The secondary outcomes are self-efficacy, self-care activity, quality of life, and glycated hemoglobin A1c. For normally distributed continuous variables, the mean difference within and between the groups will be determined by paired sample Student *t*-test and independent sample Student *t*-test, respectively. Non-parametric tests such as the Mann-Whitney *U* test, the Wilcoxon signed rank test, and the Friedman analysis of variance test will determine the median difference for variables that violated the normality assumption. A repeated measure analysis of variance will be considered to estimate the variance between the baseline, post-intervention, and post-follow-up measurements. A sample of 10 volunteers in the treatment group will participate in the qualitative interview to explore their experience with the diabetes self-management coaching program and overall feasibility. The study will follow a qualitative content analysis approach to analyze the qualitative data. Qualitative and quantitative findings will be integrated using a joint display technique.

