#### Sample size determination

A formal sample size calculation will not be applied for a feasibility RCT study [34]. Hertzog [35] suggests that a sample size of 10–40 participants per group is enough for feasibility studies (Hertzog, [35]. Hence, considering the study’s pilot nature, the intervention’s high intensity, and the limited research fund, we will recruit 40 participants. Twenty participants will be allocated to each arm of the study with a 1:1 ratio.

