### Secondary outcomes

The secondary outcomes of the study encompass self-efficacy, self-care activity, quality of life, and HbA1c. These outcomes will be assessed at baseline (T1), post-intervention (T2), and post-follow-up period (T3) (Table 2).A. Self-care activityThe diabetes self-care activity is the ability of an individual with type 2 diabetes to follow a healthy eating plan, perform regular exercise, monitor blood glucose, perform foot care, adhere to diabetes medication/s, and cease cigarette smoking [43]. Self-care activity will be measured using the Summary of Diabetes Self-Care Activity tool (SDSCA) [43]. The tool will be culturally translated and validated for face and content validity by a panel of experts.B. Self-efficacySelf-efficacy is an individual’s belief and confidence in their ability to perform intended activities that affect their life and control over how these activities are experienced [44, 45]. Self-efficacy will be measured using the Stanford Self-Management Resource Center (SMRC) diabetes self-efficacy scale, which has an eight-item Likert Scale [46]. The tool will be translated into the local language, Amharic, and undergo content validation by a panel of experts.C. Quality of lifeAs defined by the WHO, quality of life is an individual’s perception of their position in life in the context of the culture and value systems in which they live and their goals, expectations, standards, and concerns [47]. The quality of life of individuals with type 2 diabetes will be assessed by a valid and reliable WHOQOL-BREF tool [48]. The tool has demonstrated reliability and construct validity [48]. The WHOQOL-BREF tool has 26 items addressing the physical, psychological, social, and environmental health domains with five ordinal scales [48].D. Glycated hemoglobin A1CHbA1C is a reliable measure of long-term glucose monitoring recommended by the WHO and the American Diabetes Association (ADA) [49]. HbA1c < 7% is considered good glycemic control, and HbA1c equal to or greater than 7% will be regarded as an uncontrolled glucose level [50].

**Table 2 Tab2:** Outcome assessment timeline showing list of assessment items (outcomes) and corresponding evaluation time

**Outcome variables**	**Assessment time in weeks**												
	T1–W0	W1–3	W4	W5	W6	W7	W8	W9	W10	W11	W12	T2–W13	T3–W24
**Acceptability**													﻿√
Eligibility rate	√												
**Recruitment**	√												
Retention rate	√										√		√
**Adherence rate**		√	√	√	√	√	√	√	√	√	√		

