### Data analysis and management

An independent statistician will enter, code, and clean the data using Epi-Info version 7.3.2. The data will be imported to SPSS version 29 for analysis**.** The principal investigator will analyze the data in consultation with statisticians and the research team. An intention-to-treat (ITT) analysis technique will be followed to analyze the quantitative data [53]. An ITT analysis will run data of all participants irrespective of their adherence to the program [54], and missing values will be filled using multiple imputation techniques [55]. Baseline differences between the treatment and control groups will be examined using *t*-tests. Frequencies, percentages, mean, median, standard deviation, and interquartile range will be computed to describe the population. A *p*-value < 0.05% with a 95% confidence level will be used to determine statistical significance.

Differences in the effect size of the secondary outcomes of the study will be computed following a test of assumptions. For normally distributed continuous outcomes, the mean difference within and between the groups will be determined by paired sample Student *t*-test and independent sample Student *t*-test, respectively. Non-parametric tests such as the Mann–Whitney *U* test, Wilcoxon signed rank test, and Friedman analysis of variance test will be computed to determine the median difference for variables that violate the normality assumption. A repeated measure analysis of variance will be considered to estimate the variance between the baseline, post-intervention, and post-follow-up measurements. If a difference is detected between the two groups, a covariate analysis approach or multivariate analysis technique will be considered to rule out the effect of covariates using the pretest score and age of the participant as the covariate.

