## Discussion

Self-management strategies rely on individuals’ preferences, build on prior knowledge, recognize contextual factors, and encourage active engagement in chronic illness care [62]. Establishing collaboration between patients, health care providers, family members, and the community at the primary care level is a means for successful self-management of chronic illness [63]. Diabetes self-management in the primary care of Ethiopia is problematic due to poor linkage within the health systems, poor quality of services, and lack of public awareness. Individuals with diabetes may live with the illness for many years and are supposed to manage a significant portion of the self-care activities such as diet, exercise, medication, foot care, and blood glucose monitoring by themselves [63].

In resource-limited settings where community support programs and linkage are lacking, primary care agencies need to think of alternative schemes to address the self-management needs of individuals with diabetes. The practice of self-management strategies like goal setting in the primary care settings is challenged by patient readiness, skill, and attitude, provider’s attitude and skill, and lack of time [64]. Diabetes self-management coaching has shown significant improvement in self-efficacy, self-care behavior, quality of life, and clinical parameters among individuals with type 2 diabetes in developed countries. However, one of the challenges in adapting and tailoring a complex health intervention in resource-limited countries is the program’s acceptability and implementation feasibility. Hence, the current study will explore the acceptability of the DSM coaching program. Furthermore, the study will evaluate the preliminary effectiveness of the DSM coaching program on self-efficacy, self-care activity, quality of life, and HbA1c. Evidence generated from this feasibility/pilot study will be used to design and implement a definitive RCT among individuals with type 2 diabetes.

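### A normality check on about 20 people per arm decides whether each secondary outcome gets a mean difference, and the rank-test branch names no effect estimate with a confidence interval

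*Protocol article*

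**What the plan says.** Protocol article, Data analysis and management, opens the rule for the secondary outcomes with "Differences in the effect size of the secondary outcomes of the study will be computed following a test of assumptions". Two branches follow.

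- Normal branch: "For normally distributed continuous outcomes, the mean difference within and between the groups will be determined by paired sample Student" and independent t-tests, for the within-group and between-group comparisons respectively.
- Non-normal branch: Mann-Whitney, Wilcoxon signed rank and Friedman tests, "to determine the median difference for variables that violate the normality assumption".

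The Methods part of the Abstract repeats the rule: the rank tests "will determine the median difference for variables that violated the normality assumption".

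The section does not name the normality test, its level, or what it is applied to (each arm, each visit, change scores or residuals). Repeated-measures ANOVA and covariate adjustment appear only as options, and adjustment only if a group difference is found.

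Under Secondary outcomes: "The secondary outcomes of the study encompass self-efficacy, self-care activity, quality of life, and HbA1c", each measured at T1, T2 and T3. Under Sample size determination: "Twenty participants will be allocated to each arm of the study with a 1:1 ratio". The Discussion gives the purpose: "Evidence generated from this feasibility/pilot study will be used to design and implement a definitive RCT".

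**The concern.** The choice of analysis is made on the same small data set that is then analysed. With about 20 people per arm, a normality test has little power against moderate skew and still rejects some normal data, so the branch an outcome lands in is partly chance.

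The two branches do not deliver the same thing. The t-test branch gives a mean difference, to which an interval attaches directly. The rank branch gives a p-value and a label, the median difference, that the named tests do not in general estimate. Nothing else in the section guarantees a between-arm estimate, because the repeated-measures and adjusted analyses are not firm commitments.

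At stake is what the trial passes on. Planning a definitive trial needs, for each outcome, an effect estimate with an interval on a scale fixed in advance.

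**Working it through.** **Inputs from the article.** 20 per arm; four secondary outcomes; two post-baseline visits (T2, T3); a retention criterion of 80%, so 0.80 × 20 = 16 per arm. The allocation figures agree: 10 draws × blocks of 4 = 40, and 40 / 2 = 20 per arm. There is no power figure to reproduce, since "A formal sample size calculation will not be applied for a feasibility RCT study".

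**Assumptions, because the article gives none.** Shapiro-Wilk at 0.05, run either in each arm (rank test if either arm fails) or on pooled residuals; the same distribution in both arms and at both visits, with no treatment effect; T2–T3 correlation 0.5 or 0.7. There were 4,000 simulated trials per setting (1,500 for the per-arm gamma figures).

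**Step 1: how well the check sorts.** For normal data tested in two arms, the chance of at least one rejection is 1 − 0.95² = 0.0975; simulation gives 0.102. Lognormal skewness is (e^{σ²} + 2)√(e^{σ²} − 1). For σ = 0.25 this is 3.0645 × 0.254 = 0.78; for σ = 0.5 it is 3.284 × 0.533 = 1.75. Gamma with shape 4 has skewness 2/√4 = 1.

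**Step 2: different methods at T2 and T3, if the check is made per visit.** If p is the chance of the rank branch at one visit and the two verdicts were independent, the chance that they differ is 2p(1 − p). For normal data this is 2 × 0.102 × 0.898 = 0.18; for p = 0.50 it is 0.50. Correlation between visits generally lowers it. Simulated, 20 per arm:

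| Assumed scores | Rank branch at one visit, per-arm test | T2 and T3 differ, per-arm test | T2 and T3 differ, pooled residuals |
|---|---|---|---|
| Normal | 0.10 | 0.17–0.19 | 0.09–0.10 |
| Bounded 1–10 score | 0.08–0.09 | 0.14–0.16 | 0.08–0.09 |
| Bounded 0–7 day count | 0.32–0.33 | 0.42–0.44 | 0.36–0.40 |
| Lognormal, skewness 0.78 | 0.35 | 0.39–0.44 | 0.37–0.42 |
| Gamma, skewness 1 | 0.50 | 0.41–0.46 | 0.40–0.46 |
| Lognormal, skewness 1.75 | 0.76–0.77 | 0.30–0.33 | 0.27–0.29 |

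The last row is lower because strongly skewed scores usually fail at both visits. Repeat runs moved these values by a point or two. With 16 per arm and the per-arm test, the range over all these settings except the gamma, which was not run at that size, is 0.14–0.42.

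**Step 3: one check per outcome.** Both visits then share a branch and the T2/T3 difference is 0. The branch itself is still chosen from the data. As a guide from the single-visit column, about 10% of normal and 35–50% of moderately skewed outcomes would go to the rank branch.

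**Step 4: does the rank branch give a median difference?** Mann-Whitney tests whether values in one arm tend to exceed those in the other; this equals a shift in medians only if the two distributions have the same shape. Wilcoxon signed rank and Friedman work on within-person changes and ranks, so they give no between-arm quantity. An estimator that would fit, such as Hodges-Lehmann with its interval, is not named.

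**Step 5: error rates.** Over 8,000 trials at 20 per arm, the two-stage procedure had Type I error 0.050 (normal), 0.056 (gamma) and 0.061 (Beta(5,2), where the t-test alone gave 0.055). Power at a 0.8 SD shift was 0.70–0.74, against 0.70 for the t-test alone.

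**Step 6: after the fix.** The 95% interval half-width is t × √(2/n) in SD units: 2.024 × √(2/20) = 0.64 with 20 per arm, and 2.042 × √(2/16) = 0.72 with 16. Baseline adjustment multiplies this by √(1 − r²): at 20 per arm, 0.64 × 0.866 = 0.55 for an assumed baseline correlation of 0.5, and 0.64 × 0.714 = 0.46 for 0.7.

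**The case against.** Four objections deserve weight.

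- **The text may sort by outcome, not by visit.** It speaks of outcomes and variables, and the Friedman test takes all three time points of one variable together. Both fit a single check per outcome. This stands: a reader might infer that T2 and T3 will be analysed by different methods, but the article only leaves that open, so the Step 2 figures are conditional.
- **An estimate is intended in the rank branch.** The article says so and sets a 95% confidence level. A reader might infer that the plan offers only p-values there; that goes too far. What remains is that the named tests do not in general produce the stated estimate, and none that would is specified.
- **Inference is barely harmed.** Step 5 bears this out, and the t-test and Mann-Whitney agreed on significance in 91–98% of simulated trials. Inflated error is not a basis for this point.
- **These are secondary outcomes of a feasibility trial.** None is in the progression criteria (Table 1), and the feasibility outcomes are analysed descriptively, so the switch cannot alter the decision to proceed. This stands and limits the weight of the point.

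The choice of normality test and interval method could be left to a statistical analysis plan. The switch itself cannot be set aside on that ground, because the article commits to it in two places.

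**Conclusion.** The point holds as a cheap improvement to estimation and reporting. The article ties each secondary outcome's analysis to a normality check that, at this size, separates normal from moderately skewed scores poorly (about 10% against 35–50% rejected at one visit, per-arm test). It also credits the rank tests with a median difference they do not in general estimate, and guarantees no between-arm estimate with an interval for that branch.

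Inconsistent methods at T2 and T3 are a further consequence only if the check is made per visit: about 9–19% of truly normal outcomes and 37–46% of those with skewness near 1, at 20 per arm. These figures rest on the assumed Shapiro-Wilk test, level, distributions and correlations. Under one check per outcome the figure is zero.

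The documents do not support a claim of materially inflated error or of any threat to the progression decision.

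**What to change.** In Data analysis and management, and in the Methods part of the Abstract:

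- Remove the normality switch.
- State that for all four secondary outcomes, at both T2 and T3, the between-arm mean difference with a 95% confidence interval will be reported whatever the shape of the data, preferably adjusted for the T1 score in every case and not only when a difference is detected. A bootstrap interval can be named for skewed outcomes.
- Keep the rank tests as a sensitivity analysis, and delete the statement that they determine a median difference.

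Cost: a few sentences in two places and no new data, since the baseline scores are already collected. If bootstrap intervals are used, a little extra work is needed to combine them with the planned multiple imputation.

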**Fig 1 Fig1:**
[figure not shown]
Study participant flow diagram based on the CONSORT guideline [29]. Key: *T1*, *T2*, *T3* represent time of assessment, *n* number

*Treatment group:* The treatment group will attend a 12-week DSM coaching program culturally adapted from the I-change model [27], an evidence-based health coaching intervention [20]. The DSM coaching program will have six interactive group sessions, including an overview of diabetes, goal setting, dietary management, exercise, blood glucose monitoring and medication, and foot care. In addition, the DSM coaching will also include four individual home-based coaching sessions. Furthermore, a family member who is a direct care provider will have a 10-min orientation after every individual home-based coaching session with the participants.

The principal investigator, who has completed a coaching and counseling course at Queen’s University, Kingston, Canada, will facilitate the DSM coaching sessions. The coach will deliver six 2-h group coaching sessions every 2 weeks for 3 months. The coach will use interactive discussions, experience sharing, demonstration, and home-take assignments to address the program goals. The intervention group will also continue receiving the usual care in the clinic (see Additional file 1: the DSM coaching program).

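### The between-arm tests treat all 40 participants as independent although the coached arm is taught in groups; if outcomes correlate within groups, the stated errors are too small

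*Protocol article*

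**What the plan says.** The protocol article randomises individuals in blocks of four (Randomization, allocation, and blinding). "Twenty participants will be allocated to each arm of the study with a 1:1 ratio" (Sample size determination).

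Delivery differs by arm. In the treatment-group paragraph of Intervention arms of the study, "The coach will deliver six 2-h group coaching sessions every 2 weeks for 3 months", and "The coach will use interactive discussions, experience sharing, demonstration, and home-take assignments to address the program goals". The same paragraph adds four individual home-based sessions. One coach, the principal investigator, facilitates the programme. The Control group section describes usual clinic appointments and no group activity.

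Under Data analysis and management, within-arm and between-arm mean differences are "determined by paired sample Student *t*-test and independent sample Student *t*-test, respectively". The Mann-Whitney, Wilcoxon and Friedman tests serve where normality fails. Two further analyses are conditional. "A repeated measure analysis of variance will be considered to estimate the variance between the baseline, post-intervention, and post-follow-up measurements". If the arms differ, an adjusted analysis is considered "using the pretest score and age of the participant as the covariate". Coaching group appears in none of these.

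The Discussion states: "Evidence generated from this feasibility/pilot study will be used to design and implement a definitive RCT among individuals with type 2 diabetes".

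**The concern.** This is a partially nested design: individuals are randomised, and one arm is then treated in groups. Discussion and experience sharing are means by which the programme is meant to work, so people coached together may plausibly end up more alike than people coached apart. That shared component adds variance to the coached mean. The independent-samples t-test and the Mann-Whitney test have no place for it.

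At stake is the secondary objective, the potential effectiveness of coaching on self-care activity, self-efficacy, quality of life and HbA1c. With positive within-group correlation, p-values for the arm comparison are too small and confidence intervals too narrow. The plan does use p-values to declare significance. A later trial planned from these results could also overlook a group-level variance component.

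**Working it through.** **The plan's own figure.** There is no power calculation to reproduce: "A formal sample size calculation will not be applied for a feasibility RCT study". The count is consistent: 2 arms × 20 = 40, and 10 blocks × 4 = 40.

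**Inputs from the protocol.** 20 per arm; individual randomisation; group sessions in the coached arm only; independent-samples t-test.

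**Assumptions, because the protocol gives no figure.**
- Layout: one group of 20, two of 10, or four of 5. Study setting speaks of health centres in the plural, which does not settle the number.
- ICC: 0.01, 0.05 and 0.10.
- Level: two-sided 5%. The printed threshold of 0.05% does not match the 95% confidence level beside it; that is a separate matter.
- Total variance 1 in both arms, equal group sizes, zero average coaching effect, real variation between groups.

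**Formulas.** With group size m, the coached mean has design effect DE = 1 + (m − 1) × ICC; the control mean has 1. The variance of the difference is inflated by V = (DE + 1)/2, and the true standard error is √V times the independence one. The error of the nominal 5% test is about 2 × [1 − Φ(1.96/√V)].

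**Example, one group of 20, ICC 0.05.** DE = 1 + 19 × 0.05 = 1.95; V = 2.95/2 = 1.475; √V = 1.21; approximate error 10.7%.

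**Results.** The error is from 100,000 simulated trials per cell, pooled t-test with 38 degrees of freedom:

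| Layout | ICC | DE | √V | Error | 95% interval coverage |
|---|---|---|---|---|---|
| 1 × 20 | 0.01 | 1.19 | 1.05 | 6.2% | 93.8% |
| 1 × 20 | 0.05 | 1.95 | 1.21 | 10.7% | 89.3% |
| 1 × 20 | 0.10 | 2.90 | 1.40 | 16.5% | 83.5% |
| 2 × 10 | 0.01 | 1.09 | 1.02 | 5.5% | 94.6% |
| 2 × 10 | 0.05 | 1.45 | 1.11 | 7.7% | 92.3% |
| 2 × 10 | 0.10 | 1.90 | 1.20 | 10.4% | 89.6% |
| 4 × 5 | 0.01 | 1.04 | 1.01 | 5.1% | 94.9% |
| 4 × 5 | 0.05 | 1.20 | 1.05 | 6.2% | 93.9% |
| 4 × 5 | 0.10 | 1.40 | 1.10 | 7.5% | 92.5% |

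At ICC 0 the simulated error is 4.9 to 5.1%, as it should be. By the approximation, 5% becomes 10% at an ICC of about 0.044 (one group), 0.093 (two) and 0.21 (four).

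**Which variance to inflate.** The factor DE applies to the total variance. A single group shows only its within-group variance, expected to be 1 − ICC, so multiplying that by DE under-corrects: at ICC 0.10, 0.90 × 2.90 = 2.61 where 2.90 is needed. The coached mean has variance ICC × m/20 + (1 − ICC)/20 = [(1 − ICC)/20] × [1 + m × ICC/(1 − ICC)]. The second bracket is therefore the right factor for the pooled within-group variance. For m = 20 and ICC 0.10 it is 1 + 2/0.9 = 3.22, and 0.90 × 3.22 = 2.90.

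**The case against.** Several points on the other side stand.

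- The size depends on two figures that the article does not give, and its additional file on the programme, not shown here, may state group sizes. A reader might infer that the false-positive rate doubles. That needs large groups and a moderate ICC; with groups of 5 it does not happen anywhere up to ICC 0.10, and at ICC 0.02 or below the error is at most 7.4% in every layout.
- Four of the ten sessions are individual, so the upper end of the ICC range is less obviously applicable.
- The inflation is for a null of zero average effect with real group effects. If coaching affects nobody, individual randomisation keeps the test at its level.
- A reader might blame the single coach for part of the excess error. With one coach, or one group, that effect is fully confounded with treatment. It limits generalisation and cannot be estimated from these data.
- With few groups, modelling yields little. With four groups of 5, the one-way ANOVA estimate of the ICC is zero or negative in 48% of trials when the true value is 0.05 and in 40% when it is 0.10. That argues against replacing the planned test and for a sensitivity analysis.
- These are secondary, preliminary outcomes, and no criterion in Table 1 uses a between-arm p-value. A reader might also infer that too-narrow intervals will be carried into the definitive trial and leave it undersized. The Discussion says only that evidence from the study will inform that trial.

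What the objection does not remove is that the protocol names its between-arm tests, and none allows for the grouping that its own delivery model creates.

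**Conclusion.** The concern holds in conditional form. The mismatch between group delivery in one arm and tests that assume 40 independent participants is plain from the text. Any positive within-group correlation makes the stated standard error too small for inference beyond the particular groups formed. The size runs from negligible (groups of 5, ICC 0.01) to an error of about 16.5% and a standard error about 1.4 times the independence value (one group of 20, ICC 0.10). These figures rest on assumed ICCs, assumed layouts, equal variances and real group-to-group variation. They affect what can be claimed on the secondary objective; they do not affect the feasibility progression decisions.

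**What to change.** 1. State the number and size of coaching groups, and record each coached participant's group from the attendance sheets already kept.
2. Keep the planned mean difference as a preliminary estimate. Beside it, report confidence intervals in which the variance of the coached mean is (pooled within-group variance/20) × [1 + m × ICC/(1 − ICC)], for ICC 0.01, 0.05 and 0.10, with m the group size. The control mean keeps its usual variance.
3. If there are four or more groups, add as a sensitivity analysis a partially nested mixed model, with a group random effect in the coached arm only and small-sample degrees of freedom.
4. Make no significance claim from the unadjusted test. State that inference is limited to this coach and these groups, since a coach effect cannot be separated from treatment.
5. Use a range of ICCs when sizing the definitive trial.

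The cost is analysis wording and one extra variable, with no added participants, visits or staff. Intervals become wider, by about 40% in the worst case considered (one group, ICC 0.10): √1.95 = 1.40 against the independence standard error, or √(3.9/1.9) = 1.43 against the one that the t-test would be expected to report. In the second ratio, the corrected variance is 2.90 + 1 and the reported one 0.90 + 1, each over 20.

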### Participant eligibility

#### Inclusion criteria

The study includes individuals who have been attending the diabetes clinic for at least 6 months, are living in Gondar City, are taking anti-diabetic medications, have a recent HbA1c ≥ 7% (within 3 months), and are between 18 and 65 years old.

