#### Blinding

Because of the nature of the intervention, it is impossible to mask study participants and the interventionist. However, the study assessors will be masked to the group allocation. To prevent accidental disclosure by study participants, the research assistant will provide a 5-min orientation for each participant just before each data collection period. To ensure the blinding of the assessors, three data collectors who are academic staff at the University of Gondar will be recruited for each assessment time (T1, T2, and T3). One data collector will be assigned for each phase and will not have contact with the study data and participants.

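### Adjustment of the secondary outcomes for baseline is optional and triggered by the data, and within-arm tests rank equally with the between-arm comparison; the baseline-adjusted arm difference should be unconditional

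*Protocol article*

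**What the plan says.** All the relevant text is in the protocol article, Data analysis and management.

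- Baseline comparison: "Baseline differences between the treatment and control groups will be examined using" t-tests.
- Effect analysis for normally distributed outcomes: "the mean difference within and between the groups will be determined by paired sample Student" t-test and independent-samples t-test respectively. Mann-Whitney, Wilcoxon signed-rank and Friedman tests replace these where normality fails. The abstract repeats the scheme.
- Repeated-measures ANOVA across T1, T2 and T3 is something to be considered. No arm-by-time term is stated.
- Adjustment: "If a difference is detected between the two groups, a covariate analysis approach or multivariate analysis technique will be considered", using the pretest score and age.

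No contrast is named as the main one. The text does not say whether the independent t-test uses follow-up scores or change from baseline. The size is fixed under Sample size determination: "we will recruit 40 participants. Twenty participants will be allocated to each arm of the study with a 1:1 ratio". All four secondary outcomes are measured at T1, T2 and T3 (Secondary outcomes and Table 2).

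**The concern.** There are two problems.

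First, whether a baseline-adjusted estimate is produced depends on a test result, and even then on a later choice. If the trigger is a baseline difference, randomisation means it fires by chance in about 5% of trials, so the precision available from T1 is almost never used. If it is an outcome difference, the analyst sees the unadjusted result before deciding on the adjusted one.

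Second, the secondary objective is the potential effectiveness of coaching, which only a comparison between arms can address. A paired, Wilcoxon signed-rank or Friedman test within an arm does not compare arms. If both arms improve for reasons unrelated to coaching, one arm may cross the significance threshold and the other not.

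The Discussion says the evidence will be used to design a definitive trial, so an imprecise estimate or a misread within-arm change could carry forward.

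**Working it through.** **Inputs from the protocol.** 20 per arm, 40 in total (consistent with 10 blocks of 4). No effect size, SD or power is given, because "A formal sample size calculation will not be applied for a feasibility RCT study", so there is no planned power figure to reproduce. Retention of at least 80% is acceptable, that is 0.80 × 40 = 32, or 16 per arm. The significance level is printed as "value < 0.05% with a 95% confidence level will be used to determine statistical significance"; I take 0.05, two-sided.

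**Assumptions.** The baseline/follow-up correlation r, the standardised effect d and any change common to both arms are not in the document. Ranges are shown.

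**1. Variance of the arm difference.** Relative to a follow-up-score t-test (= 1), a change-score t-test has variance 2(1 − r) and ANCOVA has 1 − r². The ratio of ANCOVA to change score is therefore (1 + r)/2.

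| r | ANCOVA, 1 − r² | Change score, 2(1 − r) | ANCOVA gain over follow-up score | ANCOVA gain over change score |
|---|---|---|---|---|
| 0.3 | 0.91 | 1.40 | 9% | 35% |
| 0.5 | 0.75 | 1.00 | 25% | 25% |
| 0.7 | 0.51 | 0.60 | 49% | 15% |

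Against the follow-up-score test, the effective number per arm is 20/(1 − r²): 22, 27 and 39 at r = 0.3, 0.5 and 0.7. The 95% CI half-width falls from 0.64 SD to 0.62, 0.56 and 0.46 SD. At 16 per arm it falls from 0.72 SD to 0.70, 0.64 and 0.53 SD.

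**2. Power, noncentral t, 20 per arm (illustrative, as the trial has no power target).**

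- d = 0.5, r = 0.7: follow-up score 34%, change score 51%, ANCOVA 57%.
- d = 0.8, r = 0.6: follow-up score 69%, change score 79%, ANCOVA 86%.

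**3. The trigger (40,000 simulated trials; unadjusted test on follow-up scores; d = 0.5 for power).**

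| Rule | Type I error, r = 0.5 / 0.7 | Power, r = 0.5 / 0.7 |
|---|---|---|
| Always ANCOVA | 4.9% / 5.0% | 42% / 57% |
| ANCOVA only after a significant baseline test | 4.2% / 3.8% | 33% / 34% |
| Outcome trigger, both tests must be significant | 2.6% / 1.8% | 29% / 30% |
| Outcome trigger, either test may be claimed | 7.1% / 8.3% | not comparable, error inflated |

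**4. Within-arm tests with no treatment effect.** Suppose both arms improve by 0.5 SD of the change score. A paired t-test with n = 20 then has power 0.565. The chance that coaching is significant and control is not is 0.565 × (1 − 0.565) = 0.246, about 25%. Simulation with a common change of 0.3 to 0.5 SD of the score and r of 0.5 to 0.7 gives 17% to 24%. With no common change it is about 5%.

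**5. Could both arms change together here?** Two routes are open, each for different outcomes.

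- Interviewed scales (self-care, self-efficacy, quality of life): "One data collector will be assigned for each phase", so occasion and interviewer cannot be separated within an arm. HbA1c is retrieved from charts and is untouched by this.
- HbA1c: participants must "have a recent HbA1c" of at least 7% within 3 months. Regression to the mean follows if that qualifying value also serves as T1. The protocol does not say whether it does.

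**The case against.** The strongest reply has four parts.

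- **A between-arm test is planned, and repeated-measures ANOVA could use the baseline data.** True. The paired tests are not the only evidence, and the protocol does not tell the reader to compare significance across arms. But no contrast is given priority, and the ANOVA is optional with no arm-by-time term.
- **The t-test may be on change scores, in which case T1 is already used.** This stands as a limit on size. The gain at r = 0.5 to 0.7 is then 25% to 15%, so it would be too strong to say that the plan wholly discards baseline information.
- **The consequence is limited.** This also stands. The progression criteria in Table 1 are all feasibility measures, and no p-value decides progression.
- **A condensed article may leave model detail to an analysis plan.** Fair for the detail of a model, but here the article states the rule itself.

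A reader might infer three stronger things that the document does not support. One is that conditional adjustment itself inflates false positives: a strict baseline trigger is conservative, at about 4%. Another is that regression to the mean in HbA1c will certainly produce a spurious fall of a known size: that needs the qualifying value to be T1 and the share of this hospital's patients above 7%, and neither is stated. The third is that the plan would lose participants with a missing visit: multiple imputation is planned.

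**Conclusion.** The point holds for the secondary, preliminary-effectiveness outcomes only. Adjustment for baseline is conditional, optional and tied to an undefined difference, and within-arm tests are given equal rank with the randomised comparison.

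The loss of precision depends on the unknown correlation and on the unstated form of the t-test. At r = 0.5 to 0.7 it is 25% to 49% of variance against follow-up scores, or 25% to 15% against change scores. At r = 0.3 the gain over follow-up scores is only 9%.

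The risk of a false claim comes from two sources: choosing between unadjusted and adjusted results (about 7% to 8% type I error if either may be claimed), and reading within-arm tests as evidence of effect (about 25% discordance if both arms improve by 0.5 SD of change). The second figure rests on a common change that is possible here but not established. The change should be made; it does not threaten the trial's primary feasibility aim.

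**What to change.** For each continuous secondary outcome:

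1. Make the between-arm comparison, adjusted for the T1 value and age, the stated analysis without any condition. ANCOVA at T2 and at T3 will do, or an equivalent repeated-measures model with an arm-by-time term.
2. Report the adjusted arm difference with its 95% CI.
3. Delete the significance tests of baseline differences and the trigger sentence.
4. Report within-arm changes descriptively only, not as evidence of effectiveness.

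The cost is a change of wording. Baseline values are already collected for every secondary outcome, age is already a named covariate, and SPSS fits these models. The planned multiple imputation can stay.
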